# Effects of neoadjuvant radiochemotherapy for anorectal function in locally advanced rectal cancer patients: a study protocol for a prospective, observational, controlled, multicentre study

**DOI:** 10.1186/s12885-023-10951-x

**Published:** 2023-05-22

**Keywords:** Anorectal function, Locally advanced rectal cancer, Neoadjuvant chemoradiotherapy, Total mesorectal excision, Sphincter preservation treatments

## Abstract

**Background:**

Neoadjuvant chemoradiotherapy (NCRT) and total mesorectal excision are standard treatment regimen for patients with locally advanced rectal cancer (LARC). This sphincter-saving treatment strategy may be accompanied by a series of anorectal functional disorders. Yet, prospective studies that dynamically evaluating the respective roles of radiotherapy, chemotherapy and surgery on anorectal function are lacking.

**Patients/design:**

The study is a prospective, observational, controlled, multicentre study. After screening for eligibility and obtaining informed consent, a total of 402 LARC patients undergoing NCRT followed by surgery, or neoadjuvant chemotherapy followed by surgery, or surgery only would be included in the trial. The primary outcome measure is the average resting pressure of anal sphincter. The secondary outcome measures are maximum anal sphincter contraction pressure, Wexner continence score and low anterior resection syndrome (LARS) score. Evaluations will be carried out at the following stages: baseline (T1), after radiotherapy or chemotherapy (before surgery, T2), after surgery (before closing the temporary stoma, T3), and at follow-up visits (every 3 to 6 months, T4, T5……). Follow-up for each patient will be at least 2 years.

**Discussion:**

We expect the program to provide more information of neoadjuvant radiotherapy and/or chemotherapy on anorectal function, and to optimize the treatment strategy to reduce anorectal dysfunction for LARC patients.

**Trial registration:**

ClinicalTrials.gov (NCT05671809). Registered on 26 December 2022.

## Introduction

### Background and rationale

Rectal cancer represents an important public health problem that compromises patients’ health-related quality of life. Worldwide in 2020, the incidence of rectal cancer was 3.8%, while its mortality rate was 3.4% [1]. Currently, total mesorectal excision (TME) is the gold standard method in sphincter-preserving therapy for locally advanced rectal cancer (LARC) [2, 3]. Neoadjuvant chemoradiotherapy (NCRT) is being used in patients with LARC (T3–T4 or N0–N1), with the purpose of reducing the local recurrence rates and increasing the likelihood of sphincter preservation [4, 5]. However, NCRT, especially neoadjuvant radiotherapy, and sphincter-saving operations are always criticized to cause a series of functional disorders, including high bowel frequency, urgency, and fecal incontinence (FI) [6–9]. These functional disorders are associated with worsening patients’ quality of life (QOL) [10, 11].

Indeed, both radiotherapy and surgery may greatly disturb anorectal function [12, 13]. However, how and to which extent the NCRT and TME on the anorectal dysfunction is still unclear. Anorectal manometry is the preferred technique to provide objective evaluation about the function of anorectal since it can identify functional sphincter weakness, poor rectal compliance, and rectal sensation impairment [14, 15]. In addition, the Wexner continence score is usually used to subjectively determine the degree of FI [16, 17]. Low anterior resection syndrome (LARS) score is another tool for the subjective evaluation of anorectal function [18, 19]. Previous studies have evaluated short-term or long-term effects of NCRT and/or surgery on the anorectal function of patients with rectal cancer through anorectal manometry, Wexner continence score and LARS score [20–22]. Particularly, prospective studies dynamically evaluating the different roles of radiotherapy, chemotherapy and surgery on anorectal function are lacking. Dynamic evaluation of the anorectal function might have implications for alleviating functional disorders and improving QOL by intervening treatments for sphincter-saving patients.

### Objectives

This prospective, observational, controlled, multicentre study aims to dynamically evaluate the different roles of NCRT with surgery, neoadjuvant chemotherapy (NCT) with surgery and surgery only on the anorectal function of patients with LARC by using anorectal manometry, Wexner continence score and LARS score. In addition, the correlation between manometric findings and Wexner continence score or LARS score after different treatment regimens would be investigated.

### Methods

#### Study design and setting

The study is a prospective, observational, controlled, multicentre study of patients diagnosed with LARC. The eligible patients will be informed about the study in detail. After providing written informed consent, these patients will undergo sphincter-preserving therapies including either NCRT with surgery, or NCT with surgery or surgery only. All patients will receive anorectal manometry, Wexner continence score and LARS score before and after the treatment and at follow-up visits. The acquired data will be finally analyzed (Fig. 1).

**Fig. 1 Fig1:**
[figure not shown]
Flow diagram of the study design

#### Participants

Patients diagnosed with LARC at The Sixth Affiliated Hospital, Sun Yat-sen University and Nanfang Hospital, Southern Medical University will be assessed for suitability for inclusion.

#### Inclusion criteria

18–75 years of age.LARC with pathological diagnosis.Patient will undergo sphincter-preserving therapies.Eastern Cooperative Oncology Group (ECOG) score for performance status is 0–2.Written informed consent.

#### Exclusion criteria

Patients who have undergone pelvic surgery, such as rectal cancer surgery and gynecological procedures.Patients who have received pelvic radiotherapy.Patients with other active malignant tumors.Patients with a history of prior peri-anal abscess, anorectal trauma, and inflammatory bowel disease (IBD).Recently (less than 4 weeks) received surgery or patients with recent severe trauma.Significant cardiac disease: congestive heart failure of New York Heart Association class ≥ 2; patients with recent (less than 12 months) active coronary artery disease (unstable angina or myocardial infarction).Recent (less than 6 months) thrombosis or embolism events, such as cerebrovascular accident (including transient ischemic attack), pulmonary embolism and deep vein thrombosis.Patients with toxicity (Common Terminology Criteria for Adverse Events (CTCAE) Grade ≥ 2) caused by previous treatment that has not subsided.Women who suffered anal sphincter tear after vaginal delivery.Pregnant or lactating women.

#### Interventions

The eligible patients who voluntarily sign the consent form will undergo either NCRT with surgery, or NCT with surgery, or surgery only according to treatment guidelines. The protocol for neoadjuvant radiotherapy with conventional fractionation is as follows: 1.8-2.0 Gy per day per fraction from Monday to Friday for a total of 25 fractions and a total dose of 45–50 Gy during cycles 2–4 of neoadjuvant chemotherapy. The neoadjuvant chemotherapy scheme consisted of oxaliplatin 85 mg/m^2^ intravenously, leucovorin 400 mg/m^2^ intravenously, fluorouracil 400 mg/m^2^ intravenously, and fluorouracil 2.4 g/m^2^ for 48 h continuously intravenous infusion, to be repeated every 14 days for a total of 5–6 cycles. Surgery will be performed according to the standard total mesorectal excision principles.

#### Outcomes

Evaluations will take place at baseline (T1), after radiotherapy or chemotherapy (before surgery, T2), after surgery (before closing the temporary stoma, T3), and at follow-up visits (every 3 to 6 months, T4, T5……). Follow-up for each patient will be at least 2 years.

The primary outcome is the average resting pressure (ARP) of anal sphincter. The secondary outcomes are maximum anal sphincter contraction pressure, Wexner continence score and LARS score. We will use high-resolution anorectal manometry (Solar GI HRM; MMS, Enschede, the Netherlands) to assess the average resting pressure and maximal contraction pressure, which has proven to be adequate for clinical use [23, 24]. This test will be performed by the trained physicians. In addition, we will use Wexner continence score and LARS score to assess fecal incontinence symptoms of patients following sphincter-preserving rectal cancer surgery.

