### Allocation

The study is a prospective, observational, controlled study without randomization. Treatment decisions will be made by multidisciplinary team for eligible patients who voluntarily sign the consent form. All patients will receive evaluation of the anorectal function through anorectal manometry, Wexner continence score and LARS score before and after therapies and at follow-up visits.

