### Statistical methods

For statistical analysis of the quantitative variables with normal distribution, the mean, standard deviation (SD), median and interquartile range will be calculated. Group comparisons will be made using t tests or Mann-Whitney U test for continuous variables. Associations between the categorical variables will be tested with the Chi-Square-test or the Fisher exact test, when appropriate. Paired values (before and after therapies) will be compared for each patient using a paired t test or a Wilcoxon test. The data will be analyzed using IBM SPSS Statistics for Windows, version 27.0 (IBM Corporation, Armonk, NY, USA). A significance threshold of p < 0.05 will be adopted for all tests.

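### The aim is to separate the roles of radiotherapy, chemotherapy and surgery, but one unspecified before/after pairing and group tests that ignore T1 do not isolate them

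*Protocol article*

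**What the plan says.** The Outcomes section sets one visit scheme for everyone: baseline (T1), then "after radiotherapy or chemotherapy (before surgery, T2), after surgery (before closing the temporary stoma, T3"), then visits every 3 to 6 months. It adds that "The primary outcome is the average resting pressure (ARP) of anal sphincter", without tying that outcome to a visit.

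Under Interventions, patients "will undergo either NCRT with surgery, or NCT with surgery, or surgery only according to treatment guidelines". The Allocation section says there is no randomisation and that a multidisciplinary team chooses the treatment.

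On the aim, Objectives speaks of the "different roles of NCRT with surgery, neoadjuvant chemotherapy (NCT) with surgery and surgery only on the anorectal function", that is, three whole regimens. The Abstract and the Discussion go further. The Abstract justifies the study by the lack of prospective work on what radiotherapy, chemotherapy and surgery each contribute, and the Discussion promises to evaluate NCRT, NCT and surgery as distinct contributors.

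Statistical methods gives two analyses for continuous outcomes. For change: "Paired values (before and after therapies) will be compared for each patient using a paired t test or a Wilcoxon test". For groups: "Group comparisons will be made using t tests or Mann-Whitney U test for continuous variables". Neither names a visit, and neither uses T1 as a covariate.

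**The concern.** T2 is the visit that lets this study do more than compare whole regimens, because it splits the neoadjuvant phase from the operation. The stated analyses do not make use of that split. A single pairing labelled before and after therapies can be taken as T1 to T2, T2 to T3, or T1 to T3, and each answers a different question. The group tests compare patients whose treatment was chosen clinically, without taking account of the resting pressure they started with.

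At stake is attribution. A fall in pressure that arose before the operation could be reported as change across surgery. A before/after change in the chemotherapy group could be reported as an effect of chemotherapy. A starting difference between groups could be reported as a treatment effect.

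**Working it through.** **Inputs.** Three groups (Interventions). Targets of 134 per group, 122 evaluable (Sample size), and 402 in total (Abstract). Visits T1, T2, T3 and follow-up (Outcomes). Chemotherapy in 5–6 cycles, repeated every 14 days (Interventions).

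**The plan's own counts.** 3 × 134 = 402, as stated. T2 as worded applies to 2 × 134 = 268 patients, or 2 × 122 = 244 on the evaluable target. T1, T3 and follow-up apply to all 402, or 3 × 122 = 366. These are targets only, because allocation is not randomised.

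**What each change contains.** Write R, C and S for the mean changes due to radiotherapy, chemotherapy and surgery. Write *t* for change over the neoadjuvant interval that treatment did not cause, and L for any radiotherapy effect that appears after T2. Adding them up is a bookkeeping device, not a claim that effects are additive.

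| Change | NCRT | NCT | Surgery only |
|---|---|---|---|
| T1 to T2 | C + R + *t* | C + *t* | not applicable |
| T2 to T3 | S + L | S | not applicable |
| T1 to T3 | C + R + *t* + S + L | C + *t* + S | S |

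**Reading the paired test against the table.**

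1. T1 to T3 exists in every group and describes each whole regimen. It equals the surgical step only in the surgery-only column. In the other two (268 of 402 = 67% of planned patients) it includes the neoadjuvant phase.
2. T2 to T3 gives the surgical step in the two neoadjuvant groups. The matching step in surgery-only patients is T1 to T3, because T1 is their pre-operative value. The text does not state this rule.
3. T1 to T2 in the NCT group is C + *t*. The only other group with a post-neoadjuvant T2 is NCRT, which also received chemotherapy, so no chemotherapy-free group separates C from *t*. The interval is not trivial: 4 × 14 = 56 days from the first to the fifth cycle, and up to 6 × 14 = 84 days for six full cycles, so about 8 to 12 weeks.

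**Reading the group tests against the table.**

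1. NCRT versus NCT at T2: (C + R + *t*) − (C + *t*) = R. This isolates radiotherapy if the groups are comparable at T1.
2. NCT versus surgery only at T3: (C + *t* + S) − S = C + *t*. This is the effect of giving chemotherapy first, including any effect of the longer route to surgery, against a group that had none.
3. Both depend on comparability at T1. If two groups differ by Δ in mean T1 pressure and the later value rises by β per mmHg of T1, an unadjusted comparison carries β × Δ that is not due to treatment. Adjusting for T1 removes that term. The document gives neither β nor Δ, so no figure in mmHg follows.

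**The case against.** The strongest reply is that nothing here is an error. Patients who go straight to surgery have no neoadjuvant treatment to be assessed after, so the absence of a T2 value follows from the group definition. The protocol promises only that "All patients will receive anorectal manometry, Wexner continence score and LARS score before and after the treatment and at follow-up visits", and T1, T3 and follow-up deliver that in all three groups. The formal objective concerns whole regimens, for which a T1-to-T3 pair is coherent. The group tests can already be run for NCRT versus NCT at T2 and for NCT versus surgery only at T3. Which visits form a pair is often left to an analysis plan, and the flow diagram and the Table 1 cell marks are not visible here.

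Most of this stands. A reader might infer that a third of the study (134 of 402) suffers missing data at T2, or that the planned pairing is bound to measure something different in each group. The documents support neither: the absence is inherent, T1 serves as the pre-operative value, and the pair is not named. A reader might also infer that some or all of the 12.6 mmHg difference in Sample size (45.3 − 32.7) would be misattributed. That figure is a between-group difference at stoma closure. It says nothing about how much arose before surgery, or about the error of a within-patient change.

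The reply does not cover two things. The Abstract and Discussion promise separate roles, which whole-regimen changes do not provide. And the group tests as written do not use the T1 value that is collected from every patient. The Discussion does foresee stratifying by age, sex and stage, but that does not bring in baseline pressure.

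**Conclusion.** The point holds as a mismatch between aim and analysis. The stated tests, run as written, do not isolate the contributions of radiotherapy, chemotherapy and surgery, and they ignore T1 in a comparison that is not randomised.

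Its size is structural. A T1-to-T3 pairing mixes phases in 268 of the 402 planned patients. The T1-to-T2 change in the 134 planned NCT patients is uncontrolled for chemotherapy. Every between-group test omits baseline. No bias in mmHg can be given, because the document reports no T1-to-T2 change, no within-patient correlation and no baseline difference between groups.

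The sample-size comparison is unaffected, since it is set at stoma closure, which corresponds to T3, where all groups contribute.

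The conclusion assumes that separating the components is a real aim, as the Abstract and Discussion say, and that no unseen document already fixes these contrasts.

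**What to change.** In Statistical methods, replace the general pairing with three named contrasts, written here for resting pressure:

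1. **Surgery:** within-patient T3 minus the last pre-operative value, which is T2 in the NCRT and NCT groups and T1 in the surgery-only group. Note that radiotherapy effects appearing after T2 may remain in the NCRT figure. Every patient is operated on, so this stays a before/after change.
2. **Radiotherapy:** T2 compared between NCRT and NCT, adjusted for T1.
3. **Chemotherapy:** T3 and follow-up values compared between NCT and surgery only, adjusted for T1. State that no within-group T1-to-T2 change will be credited to chemotherapy.

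A T1-to-T3 change can stay as a description of each whole regimen, labelled as such. Adjustment for T1 does not remove confounding by other reasons for the treatment choice, and the text should say so.

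The cost is a few sentences. No visit, test or patient is added. The small downside is that the chemotherapy contrast is read only after surgery. Recruitment began in January 2023, so the contrasts should be fixed before outcome data are examined.

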### Questionnaire used in the study

The questionnaire we use are Wexner continence score (Table 2) and LARS score (Table 3), which will be writing in Chinese thus patients can use their native language.

**Table 2 Tab2:** Wexner continence score

Type of Incontinence	Frequency				
	Never	Rarely	Some- times	Usually	Always
Solid	0	1	2	3	4
Liquid	0	1	2	3	4
Gas	0	1	2	3	4
Wears pad	0	1	2	3	4
Lifestyle alteration	0	1	2	3	4

0 = normal, 1–8 = minor incontinence, 9–14 = average incontinence, 15–20 = complete incontinence.

Never = 0 (never).

Rarely = < l/month

Sometimes = < l/week,_>l/month

Usually = < l/day, _>l/week

Always = _>l/day

**Table 3 Tab3:** Low anterior resection syndrome (LARS) score

The aim of this questionnaire is to assess your bowel function. Please tick only one box for each question. It may be difficult to select only one answer, as we know that for some patients symptoms vary from day to day. We would kindly ask you to choose one answer which best describes your daily life. If you have recently had an infection affecting your bowel function, please do not take this into account and focus on answering questions to reflect your usual daily bowel function.	

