**Do you ever have occasions when you cannot control your flatus (wind)?**	
□ No, never □ Yes, less than once per week □ Yes, at least once per week	0 4 7

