**Do you ever have any accidental leakage of liquid stool?**	
□ No, never □ Yes, less than once per week □ Yes, at least once per week	0 3 3

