**How often do you open your bowels?**	
□ More than 7 times per day (24 h) □ 4–7 times per day (24 h) □ 1–3 times per day (24 h) □ Less than once per day (24 h)	4 2 0 5

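### Wexner and LARS scores are scheduled at T3, before the temporary stoma is closed, when most of their items do not test anorectal function

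*Protocol article*

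**What the plan says.** The Outcomes section of the protocol article gives one evaluation schedule for all outcomes: baseline (T1), after neoadjuvant treatment (T2), "after surgery (before closing the temporary stoma, T3", and then follow-up visits. The same section lists the endpoints concerned: "The secondary outcomes are maximum anal sphincter contraction pressure, Wexner continence score and LARS score". The abstract repeats the schedule.

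Two other sections say who completes the questionnaires. Study design and setting: "All patients will receive anorectal manometry, Wexner continence score and LARS score before and after the treatment and at follow-up visits". Allocation repeats that everyone is evaluated "through anorectal manometry, Wexner continence score and LARS score before and after therapies and at follow-up visits". Neither section makes an exception for patients with a stoma.

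The instruments are printed under Questionnaire used in the study. Wexner (Table 2) has three leakage items (solid, liquid, gas), a pad item and a lifestyle item, and is read as "0 = normal, 1–8 = minor incontinence, 9–14 = average incontinence, 15–20 = complete incontinence". LARS (Table 3) asks, among other things, "Do you ever have occasions when you cannot control your flatus (wind", "Do you ever have any accidental leakage of liquid stool" and "How often do you open your bowels". Neither form as printed offers a not-applicable answer.

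Statistical methods plans group comparisons and paired tests of values before and after therapy. Objectives adds a correlation of manometric findings with each score after the different regimens. Neither mentions stoma status.

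**The concern.** Both scores measure what happens when stool and gas reach the anus. With a diverting stoma that load is largely absent, so a low score at T3 reflects the diversion and not the sphincter. Manometry does not have this problem, because pressures can be measured with a stoma in place.

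Three analyses are exposed:

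- **Paired tests.** T3 is the only visit defined by its relation to surgery, so the change from T2 to T3 is the natural contrast for separating the effect of surgery from that of neoadjuvant treatment, which is the study's aim. If the T3 score is held low by diversion, deterioration after surgery can be hidden.
- **Correlation.** A genuine pressure reading would be paired with a symptom score that does not reflect function.
- **Group comparisons.** Treatment is chosen by a multidisciplinary team without randomisation. If the share of patients with a stoma at the assessment differs between groups, the score difference partly reflects that share.

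Follow-up visits from T4 are set at intervals of three to six months and are not tied to stoma closure, so the problem can extend into early follow-up.

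**Working it through.** **Inputs.** Item weights and bands come from Tables 2 and 3; the T3 definition comes from Outcomes. The share of patients with a stoma at T3 is not given in the article.

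**Step 1: reproduce the printed ranges.**
- LARS maximum = 7 (flatus) + 3 (liquid) + 5 (frequency) + 11 (clustering) + 16 (urgency) = 42; minimum = 0. This matches the printed upper limit of 42.
- Wexner maximum = 5 items × 4 = 20. This matches the printed upper limit of 20.

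**Step 2: score a fully diverted patient on LARS.** Assume no stool or gas passes the anus.
- No flatus, leakage, clustering or urgency, and bowel opening answered as less than once a day: 0 + 0 + 5 + 0 + 0 = 5. This is the no-LARS band (0 to 20).
- The same patient, answering the frequency item from stoma output at one to three times a day: 0 + 0 + 0 + 0 + 0 = 0.
- Weekly flatus and liquid or mucus leakage, but no urgency or clustering: 7 + 3 + 5 + 0 + 0 = 15, still no LARS.
- Weekly urgency alone, for example from mucus: 0 + 0 + 5 + 0 + 16 = 21, the start of minor LARS. The low score is therefore typical but not guaranteed.

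**Step 3: score the same patient on Wexner.** Solid, liquid and gas items: 0 + 0 + 0 = 0. Pad and lifestyle items: 0 to 4 each, so the total runs from 0 to 4 + 4 = 8, which is normal to minor.

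**Step 4: how much could be masked.** A patient who would score 30 with continuity restored (the lowest major-LARS score) and is recorded at 5 is understated by 30 − 5 = 25 points. At the lowest minor-LARS score the gap is 21 − 5 = 16 points.

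**Step 5: possible group bias (illustrative only).** Assume a mean LARS of 25 in every group among patients without a stoma, and a score of 5 with one. If a share p has a stoma, the observed mean is 5p + 25(1 − p) = 25 − 20p. Two groups with no true difference then differ by 20 × (difference in p).

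| Assumed stoma share, group A vs B | Observed mean LARS, A vs B | Spurious difference |
|---|---|---|
| 90% vs 50% | 7 vs 15 | 8 points |
| 80% vs 60% | 9 vs 13 | 4 points |
| equal shares, including 100% vs 100% | equal | 0 points |

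The shares and the mean of 25 are assumptions, not figures from the article.

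**The case against.** **Administration at T3 is inferred.** No sentence lists the instruments visit by visit. The flow diagram is not available, Table 1 covers other data, and a full protocol or CRF could mark the scores as not applicable at T3. The data management section also requires an explanation for missing data, which leaves room for such an entry. This lowers certainty somewhat. But the article has one schedule for all outcomes and twice says that all patients receive all three assessments after treatment, so the plain reading is that the questionnaires are given at T3.

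**Diverted patients need not score as normal.** A reader might infer that every diverted patient comes out as continent and free of LARS by construction. The weights do not support that: pad and lifestyle items can take Wexner to 8, and mucus-related urgency or clustering can take LARS above 20. This objection stands.

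**The direction of the paired tests is unknown.** A reader might infer that the tests would show surgery improving continence. That depends on T1 and T2 scores, which the article does not give; if they are already near the diverted score, no improvement appears. The article also does not name the T1–T3 or T2–T3 pairing. Only masking can be claimed.

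**Group bias needs a mixture.** Read literally, T3 exists only for patients with a stoma. If everyone assessed has one, the scores are uninformative in all groups but not tilted towards any. This also stands: bias between groups is a possibility that depends on unstated shares.

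**The damage is limited.** The primary outcome and the sample size rest on resting pressure, which remains measurable, and follow-up lasts at least two years.

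**Conclusion.** The point holds in a limited form. As written, the plan has two of its three secondary outcomes recorded at a visit when a stoma is in place, and does not keep those values out of the analyses. For a fully diverted patient the typical result is a LARS of about 5 (0 to 15 without urgency or clustering) and 0 on the Wexner leakage items, with a Wexner total of at most 8. This assumes that no stool passes the anus and that the patient answers the forms as printed; the 15-point case allows some flatus and mucus leakage.

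Such scores can mask postoperative deterioration and distort the correlation between manometry and symptoms. Bias between groups is possible but cannot be sized from the article; the 4- and 8-point figures only show how it would arise. It would be wrong to conclude that surgery will appear beneficial, that a particular group is favoured, or that the primary outcome is compromised. The schedule should be corrected, but the fault does not threaten the main result.

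**What to change.** 1. Keep manometry at T3 for all patients.
2. In patients with a stoma in place, mark Wexner and LARS as not applicable, at T3 and at any later visit where the stoma is still open. Take both scores at the first visit after bowel continuity is restored.
3. Record stoma status and closure date at every visit.
4. Exclude scores recorded with a stoma in place from the paired tests, the group comparisons and the correlation analysis. Recruitment began in January 2023, so apply this to scores already collected as well.

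The cost is one change to the assessment schedule and the CRF, with two fewer questionnaires at T3 for diverted patients. The downside is that these patients have no symptom score between T2 and the first visit after closure. Anyone whose stoma is never closed will have no postoperative score, so the number of such patients should be reported by group.

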**Do you ever have such a strong urge to open your bowels that you have to rush to the toilet?**	
□ No, never □ Yes, less than once per week □ Yes, at least once per week	0 11 16

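### Within-patient change in the LARS score, and less clearly the Wexner score, from a baseline with the tumour in place mixes tumour symptoms with treatment effects, and the planned group tests do not adjust for that baseline

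*Protocol article*

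**What the plan says.** The purpose given to the scores in the protocol article (Outcomes) is post-surgical: "we will use Wexner continence score and LARS score to assess fecal incontinence symptoms of patients following sphincter-preserving rectal cancer surgery".

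Their use is wider. Study design and setting states: "All patients will receive anorectal manometry, Wexner continence score and LARS score before and after the treatment and at follow-up visits". Allocation repeats this, with "anorectal manometry, Wexner continence score and LARS score before and after therapies and at follow-up visits". The visit schedule in Outcomes reads: "Evaluations will take place at baseline (T1), after radiotherapy or chemotherapy (before surgery, T2), after surgery (before closing the temporary stoma, T3", followed by visits every 3 to 6 months.

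The tumour is in place at the first two visits. The exclusion criteria rule out "Patients who have undergone pelvic surgery, such as rectal cancer surgery and gynecological procedures", so no patient has been resected at T1, and T2 is defined as before surgery.

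Two analyses in Statistical methods bear on the scores. One is within patients: "Paired values (before and after therapies) will be compared for each patient using a paired t test or a Wilcoxon test". The other is between groups: "Group comparisons will be made using t tests or Mann-Whitney U test for continuous variables". Neither names its outcomes and neither mentions adjustment. Objectives and Discussion state that manometry and the two scores, followed over time, are to show what each of the three treatment strategies does to anorectal function.

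**The concern.** A rectal tumour can itself cause bowel symptoms. If it does, a score taken before resection measures the disease as well as the function of the sphincter and rectum. Neoadjuvant treatment may shrink the tumour before T2, and surgery then removes it. Either can lower the score while anorectal function is unchanged or worse.

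Two misreadings become possible. A fall from T1 to T2 could be taken as evidence that neoadjuvant treatment spares or improves function. A small rise from T1 to follow-up could be taken as little harm, most of all in patients whose tumours were most symptomatic at the start. Because the study's aim is to separate the roles of the treatments, this matters for how the two secondary symptom outcomes are read.

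**Working it through.** The plan gives no figure on this point to reproduce. The check compares the passages and then works through the printed LARS weights.

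**1. Does the paired test cover the scores?** Statistical methods names no outcome, but its before-and-after-therapies phrase is also the one Allocation uses for collecting the scores. The scores are two of the four declared outcomes, and nothing excludes them. They are covered on the natural reading.

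**2. Can the instrument tell tumour from treatment?** The LARS items in Table 3 ask about general bowel function. The urgency item, for example, is "Do you ever have such a strong urge to open your bowels that you have to rush to the toilet". No item asks about cause.

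**3. How much of the score is exposed?** Maximum item weights from Table 3: flatus 7, liquid leakage 3, frequency 5, repeat opening 11, urgency 16.
- Maximum total: 7 + 3 + 5 + 11 + 16 = 42.
- Urgency and repeat opening, both at least weekly: 16 + 11 = 27, and 27/42 = 64%. The printed bands label 27 as minor LARS, before any resection.
- Adding 4–7 stools a day (2) and flatus less than weekly (4): 27 + 2 + 4 = 33, labelled major LARS.

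**4. What could a change look like with function unchanged?** Start from 27 with both symptoms caused by the tumour (an assumption).
- Both ease by one category: 11 + 9 = 20, a fall of 7, which moves the patient from minor to no LARS.
- Both disappear: 0, a fall of 27. This is the extreme case.

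**5. What happens to a change score at follow-up?** Two patients both score 33 after treatment. One began at 0 (change 33 − 0 = 33), the other at 27 (change 33 − 27 = 6). The outcome is the same, but the changes differ by 27 points.

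**6. Do group comparisons remove this?** Write the T1 score as F0 + U, with F0 the part due to function and U the part due to the tumour. Suppose the tumour part is zero after resection, so the later score is F1. This additive split is a simplification.
- Within one patient: change = (F1 − F0) − U.
- Between groups A and B, mean change differs by [(F1 − F0) in A minus (F1 − F0) in B] − (U in A − U in B).

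Relief common to all groups cancels, and a difference in U does not. If the groups differ by 10 percentage points in the share of patients with a wholly tumour-caused 27, mean change differs by 0.10 × 27 = 2.7 points. That difference in shares is an assumption; the document gives no such figure.

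Allocation leaves treatment choice to the multidisciplinary team without randomisation, so equal U cannot be presumed. The limitations paragraph of the Discussion foresees stratifying by age, sex and cancer stage, but not by baseline symptoms.

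**7. The T1-to-T2 interval.** The surgery-only group has no neoadjuvant interval, so it offers no parallel change over this period. The two neoadjuvant groups can be compared with each other, but may differ in tumour response.

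**8. Wexner.** Table 2 scores solid, liquid and gas incontinence, pad use and lifestyle alteration (5 × 4 = 20). It has no urgency or frequency item, so steps 3 to 5 do not carry over.

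**The case against.** The case on the other side is substantial, and much of it stands.

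- **No stated attribution.** A reader might infer that the protocol will count the whole before/after change as a treatment effect. No sentence says so. What can be said is that the change is planned evidence about treatment roles and that tumour symptoms are not mentioned as another explanation.
- **A baseline is good practice.** A reader might infer that taking LARS before resection is an error. The printed questionnaire says it assesses bowel function and no item refers to surgery, so the document gives no ground for calling it invalid at T1. The Discussion also cites an earlier study that took manometry and Wexner before and after chemoradiotherapy.
- **Symptom relief is a consequence of treatment.** If tumour response eases urgency, the patient benefits. Whether that belongs in the effect of interest is a choice of estimand, so there is no case for removing the paired comparisons.
- **Group comparisons help.** All three strategies include resection, so shared relief cancels from T1 to follow-up. It would be wrong to say that nothing offsets the problem there. What remains is imbalance between groups. The protocol admits it is not randomised, but the tests it names leave that imbalance unadjusted.
- **Detail may sit elsewhere.** Covariates are often left to an analysis plan. The point here rests on what the article does state: paired tests and unadjusted group tests, alongside a purpose that does not match the schedule.

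**Conclusion.** The point holds in limited form. The stated post-surgical purpose does not match the pre-surgical use at T1 and T2, and a within-patient LARS change from T1 cannot alone show the role of any one treatment. Up to 27 of 42 points lie in two items that a tumour could plausibly drive. For a patient scoring 27 on those two items, the examples above range from a 7-point to a 27-point fall with no change in function.

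Those figures describe what the scoring allows; they do not estimate the bias. A reader might take 27 points as the expected distortion, but the document gives neither the frequency of tumour-caused symptoms nor how far they resolve, so the actual size is unknown. The conclusion rests on two assumptions: some tumours cause these symptoms, and treatment relieves them to some degree.

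For Wexner, the mismatch of purpose and timing and the lack of baseline adjustment stand, but the argument from urgency and frequency does not. The primary outcome, resting pressure, is not affected.

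**What to change.** 1. Reconcile the purpose sentence in Outcomes with Study design and setting and Allocation, so that it covers use before as well as after surgery.
2. Keep collecting both scores at T1 and T2.
3. Make the main treatment comparison of LARS and Wexner a between-group comparison of scores after bowel continuity is restored, with the T1 score as covariate (ANCOVA or a rank-based equivalent), in place of the unadjusted t or Mann-Whitney tests.
4. Report paired T1-to-T2 and T1-to-follow-up score changes descriptively, with a statement that they include tumour effects.
5. Rely on the manometric pressures, already collected, for the T1-to-T2 question about sphincter function.

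This needs no new data or visits. Trial status puts completion at the end of December 2026, which leaves room to settle it before analysis. The costs are slightly more analysis work and a weaker symptom-score claim for the neoadjuvant phase alone. Adjusting for T1 will not remove all confounding: treatment is chosen by the clinical team, and the T1 score is itself a mixture of function and tumour symptoms.
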